**Deterioration in child since referral**

If, during a discussion about the website for some reason a caregiver raises concerns regarding a deterioration of their child’s mental health or mental health treatment, [name] will recommend the following available options to the family.

1. Discuss these concerns with their referrer (eg GP)
2. Discuss these concerns with the paediatrician, if available.
3. Discuss these concerns with national help lines (eg MCHN/Parentline) and clinical services as appropriate.

These issues will be followed up with [name]. [name] will then consider discussing these concerns directly with the family, and consider an appropriate clinical response, such as contacting the paediatrician who triaged the referral, and notify them of the parent’s concerns so they can consider an earlier review or other form of clinical support.

I will notify RCH HREC if the patient becomes distressed despite the initial procedure.

**Concern about child safety and welfare**

It is very unlikely that there will be a concern raised regarding the child safety or welfare, during the qualitative interview discussing their experience using the website. However, if a concern is raised regarding child protection notification, we are aware of our legal responsibilities, to which we are mandated as medical and psychology practitioners. In circumstances where we are concerned about the safety or welfare of the child, we may be legally required to report these concerns to the Department of Health and Human Services. This is part of [name] usual care, as a general paediatrician, and requires no change in practice. [name] has previously received formal training in child protection as part of his advanced training fellowship with the Royal Australasian College of Physicians. He has also conducted qualitative interviews with 16 parents previously (HREC 2019.160)

During the description of the research project, prior to consenting families, [name] will use the telephone script to explain that all information is confidential, and won’t be disclosed without the participants permission, “except at required by law”.

If, during the participant interview, we become concerned about the child’s safety, we will:

- Explore the participant’s available avenues of support
- Let them know we are concerned about the situation
- Ask if they would be willing to contact additional help, or if we could contact that extra help on their behalf.
- Explain that, as a researcher, we are concerned for them and their child, and would like to talk to the supervisor of the research team ([name]), to see if any additional support needs to be arranged.

Once the interview ends, [name] will contact supervisor ([name]) to discuss the interview, and our concerns, immediately. The supervisor will then decide on the best course of action, taking into account our legal and ethical obligations to the child. As a guide, we will consider our alternatives as:

- Notify child protection with concerns about children in need of protection
- Notify Child FIRST where there are concerns about a child’s wellbeing
- If appropriate, we can consult with RCH support services, such as Gatehouse, RCH social work department and RCH psychology services.

# Reporting of safety events

Although it is not expected that this intervention poses a risk of a serious adverse event, if there is a SAE, this is how it will be reported.

Any SAE occurring in a study participant will be reported to the HREC within 24-72 hours of occurrence, in accordance with the safety reporting policy of the HREC. The HREC safety reporting form will be completed, signed and submitted by an investigator.

# DATA AND INFORMATION MANAGEMENT

# Overview

[name] is responsible for storing essential trial documents relevant to data management and maintaining a site-specific record of the location(s) of the site’s data management-related Essential Documents.

[name] is responsible for maintaining adequate and accurate source documents. Source data will be attributable, legible (including any changes or corrections), contemporaneous, original, accurate, complete, consistent, enduring and available. Changes to source data (hardcopy and electronic) must be traceable, must not obscure the original entry, and must be explained where this is necessary.

[name] will also maintain accurate case report forms (CRFs) (i.e. the data collection forms) and be responsible for ensuring that the collected and reported data is accurate, legible, complete, entered in a timely manner and enduring. To maintain the integrity of the data, any changes to data (hardcopy and electronic) must be traceable, must not obscure the original entry, and must be explained where this is necessary.

# DATA MANAGEMENT

# Data generation (source data)

In this trial, the following types of data will be collected:

- personal identifying information (names, dates of birth, contact details)
- sensitive information including health data (mental health symptoms, behaviour symptoms, health service use)

The source documents for this trial include:

- surveys completed by the participant through REDCap,
- signed verbal consent forms completed by the administration staff at the clinic and [name],
- anonymous website usage data from Google analytics,
- and audio recording and hand written notes written by [name] during the semi-structured phone interviews.

# Data capture methods and data use, storage, access and disclosure during the trial

Data collection methods

Data for this trial will be collected and entered using electronic data collection forms which will be completed by the participant. Website usage data will be collected by Google analytics and manually transferred across to the relevant participant on REDCap, by [name]. Google analytics collects anonymous website usage data on websites. Hardcopy field notes from the qualitative interviews will be collected by [name]. The data will be used for the analyses specified in the protocol and Statistical Analysis Plan.

Following the completion and analysis of the trial, the data will be retained long-term following the mandatory archive period for use in future research projects (see section 9.2.5).

Storage and access

Hard copy data will be stored by the Site in a locked cabinet in a secure location, accessible to the research team only.

Electronic data will be securely stored in MCRI's REDCap database system and in files stored in MCRI's network file servers, which are backed up nightly. **Files containing private or confidential data will be stored only in locations accessible only by appropriate designated members of the research team.**

REDCap is hosted on MCRI infrastructure and is subject to the same security and backup regimen as other systems (e.g. the network file servers). Data is backed up nightly to a local backup server, with a monthly backup taken to tape and stored offsite. REDCap maintains an audit trail of data create/update/delete events that is accessible to project users who are granted permission to view it. Access to REDCap will be provided via an MCRI user account or (for external collaborators) via a REDCap user account created by the MCRI system administrator. The permissions granted to each user within each REDCap project will be controlled by, and will be the responsibility of, the trial team delegated this task by the Principal Investigator. REDCap has functionality that makes adding and removing users and managing user permissions straightforward. All data transmissions between users and the REDCap server are encrypted. The instructions for data entry to REDCap must be read and the training log signed prior to personnel commencing data entry on REDCap.

Authorised representatives of the sponsoring institution as well as representatives from the HREC, Research Governance Office and regulatory agencies may inspect all documents and records required to be maintained by the Investigator for the participants in this trial. The trialsite will permit access to such records.

Disclosure

The trial protocol, documentation, data and all other information generated will be held in strict confidence. No information concerning the trial or the data will be released to any unauthorised third party, without prior written approval of the sponsoring institution. Clinical information will not be released without written permission of the participant, except as necessary for monitoring by the HREC, Research Governance Office or regulatory agencies.

# Data confidentiality

Participant confidentiality is strictly held in trust by the research team. To preserve confidentiality and reduce the risk of identification during collection, analysis and storage of data and information, the following will be undertaken:

(1) The number of private/confidential variables collected for each individual has been minimised. The data collected will be limited to that required to address the primary and secondary objectives.

(2) Participant identifiers will be stored separately to the data collected; documents with identifiers will be stored separately to participant data. Participant data and samples will be identified through use of a unique participant trial number/code assigned to the trial participant (“re-identifiable”). The Site Principal Investigator is responsible for the storage of a master-file of names and other identifiable data with the participant ID; access to this document will be restricted to the site trial team and authorised persons as listed previously. The master file should be stored securely, and separately, from trial data in locked/ password-protected databases with passwords kept separately

(3) Separation of the roles responsible for management of identifiers and those responsible for analysing content. The data will be analysed by the statistician, who will be provided with anonymised data identified only by the unique participant trial ID.

# Quality assurance

[name] will be responsible for data cleaning and site monitoring. Site monitoring will entail weekly checks with the clinic sites to ensure no problems with identification of eligible participants, recording these participants in the internal database, and recording parental consent to pass on contact details to [name].

# Record Retention

As per the Australian Code for the Responsible Conduct of Research, study records and data will be kept for a minimum of 5 years following the completion of the study. At 5 years, we will destroy the records, including audio recordings. Records will be destroyed by deleting the data from MCRI servers, and hard copies will be disposed of within confidential waste.

# TRIAL OVERSIGHT

# Governance structure

Governance of sites and the research project will be provided through two tiers:

- [name] will meet with the supervisory team ([name], [name] and [name]) every fortnight during the trial. These meeting will run for 1 hour. These meetings will be discuss all areas of the trial, from recruitment, timelines, consent and data collection, all matters relating to the intervention, data management and safety.
- [name] will meet with the administration staff at each clinic on a weekly basis. These regular face to face meetings will allow any discussion about problems encountered in the recruitment phase of the trial.

Between these meetings, any urgent problems related to the trial can be addressed through direct communication between [name] and supervisor [name].

# STATISTICAL METHODS

# Sample Size Estimation

As this is a pilot trial, there is no consistent agreement in the number of participants required to assess acceptability and feasibility. Typically, between 20-100 participants are recruited into similar trials assessing acceptability, feasibility and usability.^12,14,28^ As a pilot RCT, the trial is not powered to assess statistical significance of parent, child or health service-related outcomes.

The quantitative primary outcomes and secondary outcomes will be compared using descriptive statistical methods. Linear regression and logistic regression will be conducted to estimate mean differences (and 95% confidence intervals) for continuous outcomes, and odds ratios (and 95% confidence intervals) for binary outcomes, respectively, between trial arms. Analyses will be adjusted for baseline scores of the outcome measure. The research team will calculate Cohen’s d effect sizes for continuous outcomes to inform sample size calculations for the planned future RCT. The RCT will be reported in accordance with the CONSORT e-health statement and we will complete an intention-to-treat analysis at the level of the child.^29^

Qualitative interviews will be analysed using an inductive content analysis approach. This approach employs three main parts: i) open coding; ii) creating categories by cross referencing, and grouping the data; and, iii) abstraction.^30,31^ Overall, we hope to describe key issues, themes and events in the parent’s experience using the FindWays website.

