# TRIAL DESIGN

# Overall design

A pilot randomised controlled trial will be implemented to assess the acceptability and feasibility of the FindWays website and compared trends in child and parent related outcomes, compared to a standard care control group,

*Design:* Pilot RCT comparing the FindWay website intervention group with a control group.

*Intervention*: FindWays website is a co-designed online service navigation platform and website providing evidence-based parenting strategies. Informed by qualitative study (HREC 2019.160) and co-design workshops, the website provides content on children’s behavioural and emotional problems. Specifically, this content includes strategies to help specific behaviour or emotional problems, describes providers and programs that can help child behavioural or emotional problems, and a list of local community services and individual professionals who can see children with a mental health care plan. Parents will have access to the intervention for 4 months.

*Control*: A standard care control group was chosen to measure the realities of trying to access paediatric help for the child’s behavioural or emotional problem. This also allows us to compare trends in efficacy of secondary outcomes between the two groups.

*Sample size:* There are no published data on the optimal size of a pilot RCT to assess acceptability and feasibility. However, prior studies conducted by this team have included between 15-30 participants in each trial arm, and the Melbourne Children’s Trial Centre has suggested a minimum of 20 participants. As such, I will aim to recruit 60 parents, with 30 in each arm.

*Setting:*Three specialist general paediatric outpatient clinics in Geelong, Victoria. There are no public paediatric outpatient clinics available to Geelong children, unless the family identifies as ATSI or migrant background. There are three private clinics available in Geelong, of which bulk billing is paediatrician dependent on a case-by-case basis.

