# Trial population

The trial population will be all eligible parents of children, aged two-12 years. with a behavioural and/or emotional problem, who are referred to a paediatric clinic for their first review. These paediatric clinics will be either Geelong Children’s Clinic, Geelong Paediatric Group or Barwon Paediatrics. The referred child can either be accepted or declined by the clinic.

We expect to recruit at least 20 parents every month for three months. This estimate is based on the high number of monthly referrals for behavioural or emotional problems in 2-12 year old to these clinics (estimated to be 20 referrals every week across the 3 clinics). Further, the number of accepted referrals who were recruited within [name]’s qualitative study (HREC 2019.160), was 5 parents per week at each study site.

No power calculation has been done as the trial is not intended to assess the effectiveness of the intervention. Typically, acceptability and feasibility trials recruit around 20 participants, though 60 will give us a stronger indication of difference in acceptability between the intervention groups, and a larger number of eligible participants for the qualitative component of the study, which ideally requires around 20 participants to reach data saturation.

Exclusion criteria are listed in the table below. These criteria are justified because: i) children with a diagnosed intellectual disability or autism spectrum disorder require specialised treatments that are not listed within the platform; ii) children in out of home care are especially vulnerable and again require specialised programs with an emphasis on attachment and trauma; iii) any child requiring an urgent review (eg high severity or possibility of medical cause) is less likely to gain benefit from the website due to the shorter time frame waiting for a paediatrician review, and may be less likely to benefit from the programs and interventions listed in the website because of the increased severity.

Parents are the sole focus of the intervention, and the only source of outcome data. Children are not directed to use the website or participate in the collection of any measures. Only one parent will be consented for each child referred to the clinic.

**Table 2**. Inclusion and exclusion criteria

| *Inclusion criteria* | *Exclusion criteria* |
| --- | --- |

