# RANDOMISATION AND BLINDING

# Randomisation and concealment mechanism

A statistician not directly involved in the analysis of the trial results will prepare the randomisation schedule. The randomisation schedule will be created by computer-generated random numbers, before the first participant has been recruited. The participant cohort will be stratified by child age (2-6yo and 7-12yo) and clinic (eg GPG, GCC and Barwon Paediatrics). Within each strata, permuted block randomisation will be used to ensure balance between the Website and control group. A randomly generated sequence of block sizes containing 2, 4, or 6 participants will be used. This will help ensure balance in numbers between Website and control groups, prevent potential confounders of age or clinic type impacting the measurement of outcomes, and prevent any predictability in Website allocation.^27^ The schedule will be held by an independent statistician, and allocation will not be revealed prematurely to [name]. Because of these procedures, the research team will be unable to predict which group the participant will be allocated to.

Both [name] and the participant will become aware of which trial arm they were allocated to after randomisation. The participant and researcher will not be blind to their intervention status because it is impossible to blind a novel website intervention to participants. The administration staff and paediatricians will not be notified by the researchers of the intervention status of the participants.

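### Randomisation is stratified by child age group and clinic but the stated models name only the baseline score, so confidence intervals for mean differences will be too wide to the extent that those factors are prognostic

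*Protocol*

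**What the plan says.** Protocol section 6.1 (Randomisation and concealment mechanism) sets the design: "The participant cohort will be stratified by child age (2-6yo and 7-12yo) and clinic (eg GPG, GCC and Barwon Paediatrics"). Within strata, "A randomly generated sequence of block sizes containing 2, 4, or 6 participants will be used". One stated purpose is to "prevent potential confounders of age or clinic type impacting the measurement of outcomes".

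Section 11.1 (Sample Size Estimation) sets the analysis: "Linear regression and logistic regression will be conducted to estimate mean differences (and 95% confidence intervals) for continuous outcomes", with logistic regression and odds ratios for binary outcomes. The covariate sentence reads "Analyses will be adjusted for baseline scores of the outcome measure". The protocol nowhere brings age group or clinic into an analysis model.

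The target is 60 parents, 30 per arm (section 4.1). There is no power or precision figure to work from: "No power calculation has been done as the trial is not intended to assess the effectiveness of the intervention" (section 4.2). Section 11.1 also plans descriptive comparisons, and Cohen's d values for planning the later trial.

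**The concern.** Age group and clinic are treated as potentially important when participants are allocated, then left out when the data are analysed. Blocking within strata keeps the arms nearly balanced on both factors, so differences between strata largely cancel out of the treatment contrast. A regression without the factors does not know this. It leaves the between-stratum variation in its residual, and its standard error describes a less efficient design than the one used.

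At stake is the width of the intervals around the mean differences in the continuous secondary outcomes (child behaviour, impact and parent mental health). In a trial of 60 these intervals will be wide in any case, and the stated model could widen them further for no benefit. The pilot is also meant to test the study design before a full trial, so a mismatch between randomisation and analysis is better corrected before it is carried forward.

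**Working it through.** **Inputs from the protocol.** Six strata (2 age groups × 3 clinics); blocks of 2, 4 or 6; 60 participants, 1:1; linear model with arm and baseline score. The protocol states no precision figure, so there is none to reproduce.

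**Assumed inputs.** R² is the share of outcome variance remaining after the baseline score that age group and clinic explain, taken from 0 to 0.30. The simulation also assumes a baseline–outcome correlation of 0.6, clinic shares of 40/35/25%, and loss of 0 or 20%. None of these is in the protocol.

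**Step 1: formula.** The baseline-only model has 3 parameters, so 60 − 3 = 57 residual degrees of freedom. Age group adds 1 and clinic adds 2, leaving 54. With balance within strata, the ratio of the adjusted to the baseline-only interval width is

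√(1 − R²) × t(0.975; 54) / t(0.975; 57), where the ratio of t quantiles is about 1.001.

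For R² = 0.10: √0.90 = 0.949, giving a ratio of 0.950. The baseline-only interval is 1/0.950 − 1 ≈ 5.3% wider.

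**Step 2: simulation.** 4,000 trials per setting with no true effect, analysed by ordinary least squares both ways. Simulated excess is the mean baseline-only width divided by the mean adjusted width, minus 1.

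| R² | Ratio (formula) | Excess width (formula) | Mean widths, baseline-only / adjusted | Excess width (simulated) | Coverage, baseline-only | Coverage, adjusted |
|---|---|---|---|---|---|---|
| 0 | 1.001 | −0.1% | 0.8303 / 0.8336 | −0.4% | 94.9% | 95.1% |
| 0.05 | 0.976 | 2.5% | 0.8320 / 0.8142 | 2.2% | 95.8% | 95.4% |
| 0.10 | 0.950 | 5.3% | 0.8321 / 0.7922 | 5.0% | 96.4% | 95.1% |
| 0.20 | 0.896 | 11.7% | 0.8334 / 0.7474 | 11.5% | 97.3% | 95.1% |
| 0.30 | 0.838 | 19.4% | 0.8347 / 0.6989 | 19.4% | 97.6% | 95.0% |

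The spread of the estimates shows the mechanism. At R² = 0.30 the empirical SD of the estimated difference is 0.1792 without the factors and 0.1754 with them. The two estimators are almost equally precise; what differs is the standard error that the model reports.

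**Step 3: 20% random loss** (2,500 trials per setting).

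- R² = 0: 0.9368 / 0.9489, so adding the factors widens the interval by 1.3%.
- R² = 0.10: 0.9419 / 0.9041, excess 4.2%; baseline-only coverage 96.2%.
- R² = 0.30: 0.9422 / 0.7978, excess 18.1%; baseline-only coverage 97.3%.

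A separate simulation with six equal strata of 10 and 20% loss gave width ratios of 0.989, 1.016, 1.046, 1.113 and 1.195 for R² of 0, 0.05, 0.10, 0.20 and 0.30, which is the same pattern.

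**Step 4: logistic model** (up to 3,000 trials, 60 participants, conditional log odds ratio 0.8, no baseline score in the model).

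| Strength of strata effects | Unadjusted: model SE / empirical SD | Adjusted: model SE / empirical SD | Mean log odds ratio, unadjusted / adjusted |
|---|---|---|---|
| None | 0.539 / 0.558 | 0.560 / 0.603 | 0.834 / 0.888 |
| Moderate | 0.536 / 0.537 | 0.579 / 0.621 | 0.772 / 0.878 |
| Strong | 0.533 / 0.488 | 0.632 / 0.671 | 0.666 / 0.887 |

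Adding the strata raises the standard error of the log odds ratio. The unadjusted standard error is conservative only when the strata effects are strong. The adjusted model estimates a conditional odds ratio, which is a different quantity, and its model standard error falls short of the empirical SD at this sample size.

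**The case against.** The strongest reply is that covariates are commonly left to a statistical analysis plan, which section 9.2.2 mentions and which is not shown. The covariate sentence in section 11.1 does not say that the baseline score is the only adjustment, so a later plan could add age group and clinic without contradicting it. That is fair as to the wording. But section 11.1 is not silent on covariates: it states a model and leaves out the factors used to randomise. Correcting the sentence removes the ambiguity.

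The second reply is that little depends on these intervals. The primary objective is acceptability and feasibility, the trial is explicitly unpowered for effectiveness, and no threshold or test hangs on the intervals. This stands, and it limits the weight of the point.

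Several stronger readings are tempting but not supported:

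- *The intervals are too wide whatever the data show.* The excess is nil at R² = 0 and about 2% at R² = 0.05. The protocol's reason for stratifying gives no prognostic strength, and the baseline score may already absorb much of any age or clinic difference.
- *The treatment effect is biased.* Randomisation protects the mean difference with or without the factors.
- *The odds ratios lose precision too.* Step 4 shows that adjustment widens their intervals and changes the target.
- *These estimates are the only between-arm results.* Descriptive comparisons and Cohen's d are also planned.
- *Loss to follow-up leaves a damaging imbalance.* With 20% random loss, baseline-only coverage stayed at about 95% or above.
- *The effect sizes for the next trial are wrong.* Section 11.1 does not say which standard deviation Cohen's d will use, and no effect on it has been shown.

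**Conclusion.** The point holds for the mean differences, conditionally. To the extent that age group and clinic are prognostic beyond the baseline score, the model-based 95% intervals are conservative: about 2%, 5%, 12% and 19% too wide at R² of 0.05, 0.10, 0.20 and 0.30, with coverage of roughly 96–98% instead of 95%. The R² range is an assumption; the direction follows from stratified blocking.

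This is an inefficiency and does not make the inference invalid. In an unpowered pilot its consequence is modest. It is still worth correcting, because the possible gain outweighs a cost that is close to nothing.

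**What to change.** In section 11.1, replace the covariate sentence with: *Analyses of continuous outcomes will be adjusted for the baseline score and the stratification factors, child age group (2–6, 7–12) and clinic (3 levels), as main effects.* Add that binary outcomes will be adjusted for the same factors where event numbers allow, and that the resulting odds ratio is conditional on them.

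The cost is one sentence and three degrees of freedom. Both factors must be known at randomisation, so no new data are needed. If they turn out not to be prognostic, the interval widens by about 1% or less (0.4% in the full-sample simulation, 1.3% with 20% loss).
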